### Emergency treatment

During the study, if a participant’s pain persists or escalates to an intolerable level, the trial will be immediately halted, and intervention will be administered promptly. Participants are allowed to take emergency analgesics, such as NSAIDs, under the guidance of a physician, with dosage adjustments made as necessary. Additionally, if participants in the SA group do not experience relief, they will be offered acupuncture treatment or other emergency interventions to ensure the safe and effective delivery of treatment. The treatment details will be meticulously documented on the Case Report Forms (CRFs) by the researchers.

### Primary outcome

The primary outcome is the efficacy rate at 10 min post-treatment. The efficacy rate is calculated as the proportion of participants whose VAS pain scores have decreased by at least 50% compared to the baseline measurement (28).

### Secondary outcomes

The secondary outcomes include the effective rate at various time points (0, 0–1, 2, 4, 6, 8 min), VAS pain score, blinding assessment (assessed by asking participants whether they received true acupuncture and their confidence in this response), and treatment effectiveness expectations scale.

The VAS is one of the most commonly used pain intensity assessment tools (Table 2) (29). The scale consists of a 10 cm horizontal line, with one end labeled as ‘0’ to indicate ‘no pain at all’ and the other end labeled as ‘10’ to represent ‘the worst imaginable pain.’ The line presented to participants only displays the two anchor points (‘0’ and ‘10’) without any intermediate numerical markings. Participants will be instructed to mark a position on the line using a pen (e.g., with a dot or an ‘x’) that best represents their current pain intensity at that moment. The VAS will be assessed seven times in total, including at baseline, 0–1 min (during treatment), 2 min (during treatment), 4 min (during treatment), 6 min (during treatment), 8 min (during treatment), and 10 min (at the end of treatment).

After the participants make their mark, the scale will be collected by trained study personnel, who will measure the distance (in millimeters) from the ‘0’ anchor to the marked point using a ruler. This process allows for precise scoring, including fractional scores (e.g., 5.5), based on the exact position of the mark.

Currently, there are no studies specifically targeting the immediate analgesic response in primary dysmenorrhea to determine the minimum clinically important difference (MCID) threshold. Therefore, we combined previous clinical experience and previous studies in acute pain patients, where a decrease of approximately 10–13 mm on the visual analog scale (VAS) can be considered the minimum clinically important difference (MCID) (30).

To ensure uniformity, participants will receive standardized verbal instructions, emphasizing that the marking should reflect their perception of pain without additional guidance or interference. The measurement will be conducted in a quiet and private setting to minimize distractions and ensure accuracy. Study personnel will systematically record the scores to maintain consistency and data integrity.

To assess participant blinding effects, participants from the Acupuncture group or SA group will be asked at the end of the treatment whether they believe they received genuine acupuncture. Additionally, they will be required to rate their confidence in the answer on a scale from 0 to 10, where 0 indicates very uncertain and 10 indicates completely certain. If the proportion of correctly identified participants does not significantly exceed 50%, the blind is considered successful (Table 3).The treatment effectiveness expectations scale assesses participants’ expectations regarding the outcomes of acupuncture treatment. Post-treatment, participants will indicate their anticipated treatment outcomes (‘effective’ or ‘ineffective’) and rate, on a scale from 0 to 10, their feelings about receiving positive treatment and the expected results (Table 3).

**Table 3 tab3:** Blinding questionnaire and treatment expectations scale.

Blinding test	
Do you think you were given acupuncture treatment or placebo acupuncture?	Yes⬜ No⬜
How sure are you on your answer on a scale of 0 to 10? (0 = very uncertain and 10 = completely certain)	___________________

Treatment expectations scale	
What do you think of the results of your treatment?	Efficiently⬜ Inefficiently⬜
How sure are you on your answer on a scale of 0 to 10? (0 = very uncertain and 10 = completely certain)	___________________

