### Recruitment and informed consent

This is a randomized controlled trial (RCT) aimed at evaluating the immediate efficacy of acupuncture in the treatment of acute PD. The study will be conducted at the Second Affiliated Hospital of Yunnan University of Traditional Chinese Medicine, with a planned recruitment of 80 participants diagnosed with PD. A public recruitment advertisement for this study will be designed to recruit the participants online or offline channels, such as the websites, and WeChat public account. Upon meeting the inclusion criteria and expressing willingness to take part in this study, participants will be required to provide written informed consent prior to the commencement of the study (Appendix 1). During the baseline period, participants will be asked to provide information regarding menstrual cycle characteristics (e.g., cycle length, regularity, duration), baseline pain threshold, prior analgesic use, and prior acupuncture experience. These variables will be collected for exploratory analysis of potential confounding effects. Participants retain the right to withdraw from the study at any point, and their personal data will be solely utilized for medical research purposes.

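### A non-significant test is taken as proof of successful blinding, the Table 3 answer boxes do not match their question, and the post-treatment expectation scale records perceived effectiveness

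*Protocol article*

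**What the plan says.** All of this stands in the Protocol article under Secondary outcomes, including Table 3.

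- **Blinding question, prose.** Participants "will be asked at the end of the treatment whether they believe they received genuine acupuncture", and "they will be required to rate their confidence in the answer on a scale from 0 to 10".
- **Blinding question, form.** Table 3 prints "Do you think you were given acupuncture treatment or placebo acupuncture", followed by two boxes, Yes and No.
- **Decision rule.** "If the proportion of correctly identified participants does not significantly exceed 50%, the blind is considered successful". The article gives no equivalence bound and names no test. It does not say whether the arms are pooled, and the confidence rating plays no part in the rule.
- **Expectation scale.** "The treatment effectiveness expectations scale assesses participants’ expectations regarding the outcomes of acupuncture treatment". On timing: "Post-treatment, participants will indicate their anticipated treatment outcomes". The Table 3 item reads "What do you think of the results of your treatment".
- **Baseline data.** Recruitment and informed consent lists menstrual-cycle characteristics and "baseline pain threshold, prior analgesic use, and prior acupuncture experience". Expectation is not in that list.

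Statistical analysis sets two-sided testing at 0.05. Sample size sets 40 participants per group.

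**The concern.** The primary outcome is a 50% fall in self-rated pain, and real and sham needling feel different: one seeks Deqi at depth, the other only touches the skin. Belief about allocation could therefore influence the result, and the Discussion relies on the questionnaire to judge whether the blinding worked.

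The decision rule turns a failure to reject 50% into a positive finding. Such a rule is easier to pass the smaller the sample. The trial could report successful blinding when a moderate difference in belief between arms is present.

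Two form problems add to this. A Yes or a No under an either/or question does not say which option the participant chose. And a question about results, asked after the session, is answered in the light of the pain relief just felt. It cannot stand in for prior expectation.

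**Working it through.** **Inputs.** 36 per group before dropout, 8% dropout and 40 per group (Sample size); 1:1 allocation (Randomization and blinding); two-sided 0.05 (Statistical analysis). The article gives no power for the blinding test, so the only planned figure to carry over is n: 36/0.92 = 39.1, rounded up to 40, and 2 × 40 = 80, as stated.

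**Assumptions.** The test is an exact binomial test of the proportion correct against 0.5, using the upper tail (0.025) of the two-sided 0.05 test. True correct-guess rates are shown as a range because the article gives none.

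**Largest count that still passes**
- Pooled, n = 80: P(X ≥ 50 | 0.5) = 0.0165 and P(X ≥ 49 | 0.5) = 0.0283. So 49/80 = 61.3% passes (exact 95% CI 49.7% to 71.9%).
- One arm, n = 40: P(X ≥ 27 | 0.5) = 0.0192 and P(X ≥ 26 | 0.5) = 0.0403. So 26/40 = 65% passes (exact 95% CI 48% to 79%).

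**Chance of declaring success**, P(X ≤ 49) pooled or P(X ≤ 26) for one arm:

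| True correct rate | Pooled, n = 80 | One arm, n = 40 |
|---|---|---|
| 60% | 63% | 79% |
| 65% | 28% | 56% |
| 70% | 6% | 30% |

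If the rule were applied by arm and both arms had to pass at the same true rate, the chances are 0.789² = 62%, 0.559² = 31% and 0.297² = 9%.

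**What these rates mean.** With equal arms, pooled correct rate = 0.5 + (difference between arms in the proportion believing they had real acupuncture)/2. So 60%, 65% and 70% correspond to differences of 20, 30 and 40 percentage points.

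**Sensitivity.** Reading the word *exceed* as a one-sided 5% test moves the pooled limit to 47/80, with success declared 45%, 15% and 2% of the time; for one arm the limit is 25/40, with 68%, 43% and 19%. With 72 completers and the two-sided level, the pooled figures are 62%, 28% and 7%.

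**Pooled or by arm.** The choice can reverse the conclusion. Suppose 30% in each arm believe they had real acupuncture. Then 30% are correct in the acupuncture arm and 70% in the sham arm. The pooled rate is 50%, and the rule passes 99% of the time. Tested alone, the sham arm would fail 70% of the time.

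**The two questions side by side.** The prose asks whether the participant believes the acupuncture was genuine. Yes and No answer that, and each can be scored against allocation. Table 3 asks which of two treatments was given, and Yes or No does not choose between them.

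**The expectation item.** The scale is described as measuring expectations, but both its timing (after treatment) and its wording (results of treatment) describe an experienced outcome.

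**The case against.** Several stronger readings are tempting, and the documents do not support them.

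- *Neither measure can work.* The pooled test detects 94% of cases at 70% correct and 72% at 65%. It is weak against moderate unblinding, not useless.
- *The answers cannot be scored.* The prose question can be scored from Yes/No. Table 3 contradicts it and may be a translation slip, so the two need reconciling.
- *Uncertain participants are forced into plain guesses.* The 0 to 10 confidence rating already records uncertainty, although the success rule ignores it. A *do not know* box is optional.
- *These items are the only evidence against a belief effect.* The article also uses the same device in both arms and separate rooms, and collects prior acupuncture experience for exploratory analysis.
- *An expectancy analysis would condition on the outcome.* No such analysis is described, and the article does not present the expectation scale as a test of the sham.
- *Pooling hides unblinding when the arms show opposite correct rates.* In the 30%/70% example above, belief is the same in both arms. The example shows that the rule is undefined, not that unblinding is concealed.

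Two further points stand. The guess is made at the end of treatment, and Sample size anticipates mean pain changes of 4.21 and 2.15, so correct guesses may partly reflect relief and not a failure of the sham. And Figure 1, the schedule, is not available here, so an additional baseline expectation measure cannot be fully ruled out; the text, however, says post-treatment. The choice of a blinding index could be left to an analysis plan, but the pass/fail rule is stated in this article and needs changing here.

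**Conclusion.** The point holds in three limited parts.

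1. The success rule is wrong as written. At the planned size and two-sided 0.05, it would declare success 63% of the time at a true 60% correct and 28% at 65% if pooled (79% and 56% for a single arm). These figures rest on an exact binomial test and assumed true rates. The pooled or by-arm reading is left open.
2. The Table 3 blinding item contradicts the prose, so a tick on the printed form is ambiguous.
3. The scale labelled expectation measures perceived effectiveness.

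All three concern secondary outcomes and how the trial's blinding will be described. The primary analysis is not affected. The changes should be made, but nothing here stops the trial.

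**What to change.** - Delete the rule that declares success on non-significance. Report guesses by arm with 95% confidence intervals, for example Bang's index per arm, together with the confidence ratings already collected. With two answer options the index is 2p − 1, where p is the proportion correct in the arm; 26/40 would give 2 × 0.65 − 1 = 0.30, with interval 2 × 0.483 − 1 = −0.03 to 2 × 0.794 − 1 = 0.59.
- State in the report that guesses made at the end of treatment may partly reflect pain relief.
- Make the Table 3 options match the question: real acupuncture or sham acupuncture, with *do not know* as an option if wanted. Use the same wording in the prose.
- Rename the post-treatment item perceived effectiveness. If expectation is wanted, ask it before needling, worded as expected benefit.

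The cost is one case report form page and a few sentences of analysis text. Dropping the rule and renaming the item need no new data. Participants already enrolled will have completed the old form, so the report should say how many used each version.

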### Sample size

Based on previous study (31) and our past clinical treatment experience, we anticipate that after 10 min of acupuncture treatment, the mean change in VAS score in the acupuncture group will be 4.21 (SD = 1.0), whereas the mean change in VAS score in the sham acupuncture group will be 2.15 (SD = 1.0). With *α* = 0.025 (unilateral, significance level), *β* = 0.1 (type II error rate, or power = 90%), *Δ* = 1.3 (minimum clinically important difference, this is equivalent to a difference of 13 mm on the visual analog scale, which represents the minimum clinically significant change in acute pain.), and 
k
=1 (allocation ratio) (30). The sample size was calculated based on the following formula:

$$n_{C}=\frac{{\left(Z_{1-\alpha }+Z_{1-\beta }\right)}^{2}\sigma^{2}{\left(1+\frac{1}{k}\right)}^{2}}{{\left(\mu_{T}-\mu_{C}-\Delta \right)}^{2}}$$

$\mu_{T}$
: trial group mean; 
$\mu_{C}:$
 control group mean; 
σ
: standard deviation (assuming equal standard deviations for both groups).

Based on the calculations, each group will require at least 36 participants (32). Taking into account an 8% dropout rate, the adjusted sample size will be 40 participants per group. Therefore, we plan to recruit at least 80 participants for this study.

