### Statistical analysis

The statistical analysis will be conducted using SPSS 28.0 software. Qualitative data will be represented in percentages or proportions, and quantitative data with a normal distribution will be presented as the mean ± standard deviation, while non-normally distributed data will be expressed as the median and interquartile range. When analyzing variables measured at multiple time points, a repeated measures analysis of variance (ANOVA) will be used. To correct for multiple comparisons, Bonferroni correction will be applied. Effect sizes and 95% confidence intervals (CI) will also be calculated. Analysis of other variables will include independent t-tests or Wilcoxon rank-sum tests, chi-square test or Fisher’s exact tests. The Intention-to-Treat (ITT) principle will be applied to assess baseline characteristics and primary and secondary outcomes. For participants who drop out of the study, missing data will be addressed using multiple imputations by chained equations (MICE), provided the missingness is determined to be missing at random (MAR). This approach aims to ensure the robustness of the analysis and minimize potential biases introduced by missing data. All adverse events (AEs) will be compared between groups using the chi-square test or Fisher’s exact test. A two-sided test will be utilized, with a significance level *p*-value set at 0.05.

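### The stated 90% power is for mean VAS change against a 1.3 cm margin, so it does not describe the primary analysis, which is a 50% responder rate

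*Protocol article*

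**What the plan says.** **Primary outcome section.** "The primary outcome is the efficacy rate at 10 min post-treatment", defined as "the proportion of participants whose VAS pain scores have decreased by at least 50% compared to the baseline measurement". The abstract names the same outcome. The Secondary outcomes section places the VAS score itself among the secondary measures ("VAS pain score, blinding assessment").

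**Sample size section.** The planning values are means, not proportions: "the mean change in VAS score in the acupuncture group will be 4.21 (SD = 1.0" and "the mean change in VAS score in the sham acupuncture group will be 2.15 (SD = 1.0". Alpha is "0.025 (unilateral, significance level" and power is 90%. Δ is 1.3, and the protocol says that "this is equivalent to a difference of 13 mm on the visual analog scale". In the formula Δ is subtracted from the expected difference in means. The result is 36 per group, raised to 40 for 8% dropout, so 80 in total.

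**Statistical analysis section.** Repeated measures ANOVA is planned for variables measured at several times, and t, Wilcoxon, chi-square or Fisher's exact tests for the others, with effect sizes and 95% confidence intervals. On the testing level: "A two-sided test will be utilized, with a significance level" of 0.05. The figure 1.3 does not appear in this section.

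**The concern.** The calculation and the primary comparison differ in two ways. The endpoint differs, because a mean change is used to size a trial whose primary outcome is binary. The hypothesis also differs, because subtracting Δ makes the null a difference of at most 1.3 cm, whereas the analysis section describes ordinary tests with no margin.

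A reader will naturally attach the 90% to the primary outcome. A non-significant responder comparison could then be reported as a negative result from a trial with 90% power, although the article gives no basis for that figure. In the other direction, suppose the mean VAS difference is significant but its confidence interval includes 1.3 cm. The article does not say whether the superiority for which the trial was sized has then been shown.

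**Working it through.** **1. Reproducing the 36.** Inputs from the Sample size section: means 4.21 and 2.15, SD 1.0, Δ = 1.3, one-sided α = 0.025, power 90%, k = 1.

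- Distance from the margin: 4.21 − 2.15 − 1.3 = 0.76.
- n = 2 × (1.96 + 1.2816)² × 1.0² / 0.76² = 36.4 per group, in line with the stated 36.
- At 36 per group the power of this test is 89.7% by the normal approximation and 89% by noncentral t.
- Dropout: 36 / 0.92 = 39.1, so 40 per group.

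This uses (1 + 1/k) to the first power. The printed formula squares that term and would give 72.8. That is a separate point, but it confirms that 36 comes from the standard test of two means against a margin.

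**2. The same means without the margin.** The difference is 2.06. The normal formula gives 2 × (1.96 + 1.2816)² / 2.06² = 4.95. The planned test is a t-test, and by noncentral t the power is 81% with 5 per group, 89% with 6 and 94% with 7. About 7 per group would be enough, so the 36 comes from the margin.

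**3. What the planning values imply for the primary outcome.** The protocol gives no responder rates, so they have to be derived under assumptions:

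- baseline VAS b is uniform on 4 to 9 (the range is from the inclusion criteria, the uniform shape is assumed);
- change is normal with the stated means and independent of baseline;
- SDs other than 1.0 are assumed, to show sensitivity.

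A participant responds if the change is at least b/2, so the rate is the average over b of P(N(μ, SD) ≥ b/2). Power is by exact enumeration of the chi-square test, two-sided 0.05, 36 per arm.

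| SD of change | Acupuncture | Sham | Power |
|---|---|---|---|
| 1.0 (protocol) | 78% | 19% | >99.9% |
| 1.5 (assumed) | 72% | 26% | 98% |
| 2.0 (assumed) | 67% | 30% | 89% |
| 2.5 (assumed) | 64% | 34% | 74% |

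**4. Responder rates assumed directly, 36 per arm.**

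| Acupuncture vs sham | Chi-square | Fisher's exact |
|---|---|---|
| 56% vs 20% | 90% | 85% |
| 68% vs 30% | 91% | 86% |
| 60% vs 30% | 73% | – |
| 60% vs 40% | 38% | – |

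With chi-square, 90% power needs a difference of about 36 to 38 percentage points when the sham rate is 20% to 40%. At a sham rate of 10% about 33 points is enough, and at 5% about 28. With Fisher's exact test, the 36 to 38 point differences carry about 82% to 86% power.

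**The case against.** The best defence is that the trial is well powered on its own assumptions. With the stated means and SD 1.0, responder power exceeds 99.9%, and it is still 98% at SD 1.5. It drops below 90% only at SDs or rates that no document states. This stands. A reader might infer from the mismatch that the trial is underpowered for its primary outcome, and the documents do not support that inference.

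A second defence is that the planned output can serve the margin hypothesis. A one-sided 0.025 test against 1.3 is the same as checking whether the lower limit of a two-sided 95% interval exceeds 1.3, and 95% intervals are promised. A decision rule may also sit in an analysis plan that is not shown. This stands too, so it would be too strong to say that the margin cannot be tested. What can be said is that the article uses 1.3 for sizing and its analysis section makes no comparison with it. An unseen analysis plan would not cure the main defect, because the published calculation concerns an outcome that the article itself calls secondary.

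Two other readings should be set aside. The one-sided 0.025 and the two-sided 0.05 use the same critical value, so sidedness is not the source of the mismatch. A reader might also argue that 13 mm is a within-patient decrease misused as a between-group margin. The Secondary outcomes section does describe a decrease, but whether the figure supports a between-group use depends on a cited source that is not shown.

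**Conclusion.** The point holds as a mismatch between the stated power and the primary analysis. The 36 per group and the 90% arise from a test of mean VAS change against 1.3 cm, while the primary outcome is a responder proportion for which the article gives no planning rates. The primary test is read from the general analysis text, since that section does not name it.

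The size of the defect cannot be given as one number. At 36 per arm, responder power runs from about 38% (60% versus 40%) to over 99.9% (rates implied by the protocol's own means and SD). The implied rates rest on a uniform baseline and on normal change independent of baseline. The second of these is doubtful on a bounded scale, where a low baseline limits the possible fall. The conclusion is that the 90% is unsupported for the primary outcome, not that 80 participants are too few.

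**What to change.** Keep N = 80 and rewrite the Sample size paragraph for the responder outcome:

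1. State the assumed responder rate in each arm, with a rationale that does not draw on this trial's outcome data, and explain why a difference of that size is plausible and worth detecting.
2. Name the primary test, chi-square or Fisher's exact.
3. Give the resulting power, or the detectable difference, at 36 evaluable per arm. An example: with chi-square, 90% power for a difference of about 36 to 38 percentage points if the sham rate is 20% to 40%, and about 82% to 86% for the same differences with Fisher's exact test.
4. Either remove the 1.3 margin, or add to the Statistical analysis section that the mean VAS claim requires the lower 95% confidence limit of the 10-min between-group difference to exceed 1.3 cm.

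An alternative would be to make mean VAS change against the 1.3 cm margin the primary analysis. That changes the primary outcome of a registered trial and is the larger step.

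The cost of the recommended change is protocol or analysis plan wording, with no extra participants. It should be dated and made before unblinding. The consequence to accept is that the stated power will be tied openly to a large responder difference.
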